**10. Biometry**

Examining the correlation between driving behavior and cognitive assessment in patients with neurological disorders studies indicate an average to large effect sizes for the TMT (part A and B) and visuospatial tests such as the Judgement of Line Orientation Test16,17,22,45. Therefore it can be assumed that TMT-L (part A and B) and LAT can predict driving behavior with an average effect size. The calculated sample size of N = 80 results as follows: Supposing a power (1 – β) of 80% and an alpha-level of α = .05 a sample size of N = 77 is necessary to detect an average effect calculating a multiple regression with three predictors (TMT-L part A, part B and LAT). In case of early dropouts we calculate a sample size of N=80 for recruitment.
Data will be analysed by means of multivariate analyses of variances followed by post-hoc-t-tests as well as regression analyses evaluating the predictive validity of the individual tests.
Premises of statistical calculations – such as normal distribution of sample or homogeneity of variance – shall be checked upfront.

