**Study protocol not AMG/ not MPG**

**Summary**

In the light of demographic change the number of elders in road traffic increases. A variety of age related illnesses like dementia, cardiovascular or musculoskeletal diseases lead to impairments in driving related motoric but also cognitive functions like attention, visuospatial perception, reaction speed, decision-making ability and memory1-3. Studies could show that with increasing loss in functions mentioned above the risk of driving errors and accident frequency in road traffic also rises4,5. The assessment and counselling of patients in clinical practice with regard to driving safety is often associated with uncertainties also due to a lack of appropriate assessment tools6,7. Hence there is a distinct necessity of valid assessment instruments examining driving safety in elder patients.

In cooperation with Schuhfried (GmbH) from Mödling/Vienna and the Neuropsychological Department of the kbo-Inn-Salzach-Klinikum in Wasserburg/Inn, an economical, in clinical routine practice easily applicable assessment tool for driving safety will be conceptualized and validated on the basis of an on-road driving observation. For this purpose a sample of 40 healthy subjects and 40 subjects with mild cognitive impairment, all with a minimum age of 50 years, will be targeted.

At the beginning driving related cognitive functions like attention and executive functions will be comprehensively examined by means of established neuropsychological assessment instruments. Subsequently the on-road driving observation will be carried out, following a detailed protocol, in a driving instruction vehicle, with a licensed driving instructor. The assessment will be supplemented by driving specific anamnesis and questionnaires for self-assessment of driving safety. It should optimally be finished within one day. Construct validity, criterion-related validity as well as predictive value will be determined by means of the results from neuropsychological examination and the on-road assessment.

**1 Study title, version number, version date**Validation of a test set for assessment of driving safety of patients with cognitive impairment – „DRIVESC2“, version number: 1, version date: 06/04/2018

**2. Study direction, foundation**Principal investigator: PD Dr. rer. nat. [name]

Deputy principal investigator: [name]. med. [name]

Project coordination: [name], Psychologist (M.Sc.)

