(3) We expect the newly developed screening-tool to differentiate with high diagnostic accuracy between safe and unsafe drivers. The accuracy is estimated at a minimum of 80% and should exceed the accuracy of single neuropsychological tests.
(4) Besides it is expected that driving competence will additionally be predicted by factors like age, driving experience in years and mileage per year.

**4. Study aims**The aim of the study is to develop a screening-tool with high predictive validity regarding driving ability of cognitively impaired subjects. Construct validity and criterion-based validity should be tested through a standardized on-road assessment as well as cognitive neuropsychological tests proximal and distal to the construct. The high practical relevance results from the necessity of a screening-tool for driving ability which is economically, validly and reliably applicable, tablet-based and thus mobile usable in medical care practice to support a low-threshold, qualitatively valuable and safe assessment of fitness to drive and counselling with respect to mobility; not least to meet legal requirements on the practitioner’s and patient’s side in this field.

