**6. Study design**
The study is designed as a monocentric, non-randomized cross-sectional-study at the kbo-Inn-Salzach-Klinikum Wasserburg/Inn. Cut-off-scores in the MMSE of < 27 and ≥ 18 allocate the participants to the experimental group of subjects with mild cognitive impairment. Subjects with a MMSE-score ≥ 27 will be assigned to the healthy control group. We expect the recruitment period to last about 24 months. Each of these groups undergo the same assessment procedure. Blinding is only possible for the driving instructor.

**7. Study population**Women and men with an age ≥ 50 years, who possess a valid driver licence and who are active drivers, i.e. have been driving regularly the last three month before participation, and speak fluently German language can participate in the study. Regarding possible use of medication an exact documentation and clarification of potential adverse effects on on-road driving should be carried out in the context of anamnesis. Subjects who are under dose escalation or medication shifts will be excluded. The consent ability has to be checked, doubts about it also lead to exclusion. 40 subjects with mild to moderate cognitive impairment and 40 healthy control subjects will be assessed, parallelized regarding age, education, sex, driving experience and mileage per year.

*General exclusion criteria for all participants (based on annex 4, statutory order of driving licences)*

- Current severe dementia (MMSE < 18)
- Current severe psychiatric, neurological or internistic disease
- Visual impairment (visual acuity worse than 60%; visual field <140°, double-vision, hemi-neglect)
- No fluent German in speech and writing

*Specific criteria for the experimental groups*Healthy subjects (CG):

- ≥ 50 years
- German as first language respectively German-speaking since early childhood
- MMSE ≥27
- No record of severe psychiatric or neurological diseases
- Currently no internistic disease
- Currently no radio- or chemotherapy for cancer treatment

Cognitively impaired subjects (EG):

- ≥ 50 years
- First language German respectively German-speaking since early childhood
- MMSE ≥18 and <27
- Patients from the following ICD-10 diagnosis groups
  - Organic, including symptomatic disorders (F00-F09), N=20
  - Affective disorders (F30-F39), N=10
  - Schizophrenia, schizotypal or delusional disorders (F20-F29) / Neurotic, stress-related and somatoform disorders (F40-F48), N=10

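### The matching variables, three of which hypothesis 4 also names as predictors, appear in none of the models in section 10; adjusting for them costs almost nothing

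*Protocol*

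**What the plan says.** Protocol section 10 (Biometry) gives the analysis in one sentence: "multivariate analyses of variances followed by post-hoc-t-tests as well as regression analyses evaluating the predictive validity of the individual tests". It names no covariate.

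The same section sizes one model: "a sample size of N = 77 is necessary to detect an average effect calculating a multiple regression with three predictors", the three being "TMT-L part A, part B and LAT". The error levels are given as "Supposing a power (1 – β) of 80% and an alpha-level of α = .05", and recruitment is rounded up: "In case of early dropouts we calculate a sample size of N=80 for recruitment".

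Three other places bear on this:

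- Sections 6 and 7: the study is non-randomized, groups are formed by MMSE score, and the two groups of 40 are to be "parallelized regarding age, education, sex, driving experience and mileage per year".
- Section 3, hypothesis 4: "driving competence will additionally be predicted by factors like age, driving experience in years and mileage per year".
- Section 5, secondary outcomes: sociodemographic, clinical and driving-specific data are to be analysed for their influence on predicting driving behaviour. No model is attached to this in section 5 or section 10.

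**The concern.** The protocol treats age, experience and mileage as important twice: it matches on them, and it expects them to predict the outcome. The analysis it names uses them nowhere.

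For hypothesis 1 (the groups differ on the road), a t-test that ignores variables on which the groups were balanced has the wrong standard error. Close balance makes it too large. Imperfect balance, which is likely with five variables and 80 people, leaves part of the group difference attributable to the covariate. Either way the precision that the covariates could buy is lost.

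Hypothesis 4 is about what the driver factors add to the cognitive tests. That can be read only from a model holding both, and the only regression whose predictors are listed holds the three tests alone.

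**Working it through.** **Inputs from the protocol.** Alpha 0.05, power 80%, three predictors, N = 77 raised to 80 (section 10); 40 per group (Summary, section 7).

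**Assumed, because the protocol gives no figure.** An average effect is read as f² = 0.15. The standardized group difference d, the share of driving variance R² explained by the covariates, the covariate–driving correlation ρ and the residual imbalance D are also assumed.

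**1. The plan's own figure.** Overall F test in multiple regression, noncentrality λ = f²·N, degrees of freedom u = 3 and v = N − 4.
- N = 77: λ = 0.15 × 77 = 11.55, v = 73, power 0.802. N = 76 falls just short of 0.80, so the stated 77 reproduces.
- N = 80: λ = 12.0, v = 76, power 0.819.

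**2. The three tests after adjustment.** F test of the R² increase, u = 3, v = N − 1 − (3 + c) with c covariates, partial f² = 0.15.

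| Covariates c | Power at N = 77 | Power at N = 80 |
|---|---|---|
| 0 | 0.802 | 0.819 |
| 3 (age, experience, mileage) | 0.801 | 0.818 |
| 5 (all matching variables) | 0.800 | 0.818 |

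The required N stays at 77. The reverse test, of the three driver factors given the three tests, has the same degrees of freedom and also needs 77. Only an overall test of all six predictors together at f² = 0.15 would need more (N = 98; power 0.69 at 80), and neither hypothesis 2 nor hypothesis 4 requires that test.

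**3. Power of the group contrast, 40 per group.** Unadjusted: noncentrality d·√(n/2) = 0.5 × √20 = 2.236 on 78 df, power 0.60. Adjusted, with balanced covariates: replace d by d/√(1 − R²).

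| R² | Noncentrality | Power |
|---|---|---|
| 0.1 | 2.236/√0.9 = 2.357 | 0.64 |
| 0.2 | 2.236/√0.8 = 2.500 | 0.69 |
| 0.3 | 2.236/√0.7 = 2.673 | 0.75 |

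These hold to two decimals whether 3, 4 or 5 degrees of freedom are spent. At d = 0.8 the gain is small: 0.94 unadjusted against 0.96, 0.98 and 0.99.

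**4. Type I error of the t-test that ignores the covariate.**
- Close matching: the true variance of the difference is (1 − ρ²) times the variance the t-test assumes, so the actual level is about 2·[1 − Φ(1.96/√(1 − ρ²))].
- Residual imbalance of D standard deviations in one covariate: bias ρ·D, noncentrality ρ·D·√20. For ρ = 0.4 and D = 0.3 that is 0.12 × 4.472 = 0.537.

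| ρ | Close matching | D = 0.3 | D = 0.5 |
|---|---|---|---|
| 0.3 | 0.040 | 0.07 | 0.10 |
| 0.4 | 0.032 | 0.08 | 0.14 |
| 0.5 | 0.024 | 0.10 | 0.20 |

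The nominal level is 0.05 throughout. Adjustment helps in both situations.

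**The case against.** The strongest reply is that covariate lists and order of entry usually belong in a statistical analysis plan, which may exist and is not at hand. Section 10 names families of methods and never says that the comparisons are unadjusted. This has weight: the point is not that a covariate list is missing. What stands is that the methods section 10 does name, MANOVA with t-tests and a regression on three tests, do not use the design and hypothesis stated elsewhere in the same document.

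Other parts of the reply are right, and they limit the point:

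- A reader might infer that each test is examined only singly. The sized regression is joint in three tests.
- A reader might infer that hypothesis 4 is left untested. Section 5 commits to analysing these data for prediction and section 10 lists regression, so what is absent is a model linking the two.
- A reader might infer that tests correlated with age would be spurious predictors. The aim in section 4 is a screening tool with predictive validity, and a test that predicts partly because it tracks age still predicts. The increment over age is a further question.
- Mileage is a doubtful adjuster for the group contrast. The TQ-Drive questionnaire records it alongside driving difficulties and avoidance (section 8), so low mileage may be a consequence of impairment, and adjusting for it could remove part of the group difference.
- Matching already reduces confounding. If it is close, the t-test errs on the safe side. That answers the worry about false positives but not the loss of power.

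**Conclusion.** The point holds as an improvement at almost no cost, not as an error. Section 10 gives no model containing the variables that the protocol matches on and expects to predict driving.

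For the group comparison at d = 0.5, adjustment would raise power from 0.60 to between 0.64 and 0.75 for a covariate R² of 0.1 to 0.3. It would also protect against a false-positive rate of about 7 to 10% at an imbalance of 0.3 SD, for correlations of 0.3 to 0.5. All of these inputs are assumed. The gain shrinks if the true difference is large or the covariates explain little.

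It would be tempting to conclude that the sample size is wrong or that more participants are needed. The documents do not support that: N = 77 reproduces under the usual reading of an average effect and still suffices after 3 to 5 covariates.

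**What to change.** In section 10:

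1. Replace the post-hoc t-tests by group contrasts from ANCOVA/MANCOVA adjusted for age, sex, education and driving experience. Show them with and without mileage, and give the unadjusted results as a sensitivity analysis.
2. Fit one regression with TMT-L part A, TMT-L part B, LAT, age, driving experience and mileage. Report, with confidence intervals, the R² increment of the tests given the driver factors (hypothesis 2) and of the driver factors given the tests (hypothesis 4). A single order of entry would give only one of the two.
3. Keep the unadjusted predictive validity of the tests, since the screening aim needs it.

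The cost is a few sentences and 3 to 5 degrees of freedom. No extra participants are needed. Nor are extra data: all five variables must be known for the matching, and mileage is already recorded in TQ-Drive.

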**11. Data management**
All data collected in the context of the study exclusively serve research purposes, are kept in confidence and are anonymized irreversibly after elicitation plus are saved for an indefinite period. The results will be analysed after finalization of the study and will be published in anonymized manner which prevents inference to the participant’s person.

**12. Insurance**
The study is covered within the framework of the [employer's](https://www.dict.cc/?s=employer%27s) [liability](https://www.dict.cc/?s=liability) [insurance](https://www.dict.cc/?s=insurance) as well as the driving school’s insurance.

